## 2. Study Aims:

We propose to conduct a multisite, prospective, cluster-randomized trial, broadening and deepening our prior work on recognition of pediatric elevated BP, which will test methodologies to ensure every pediatric patient is screened, and if HTN or EBP are present, diagnosed and managed appropriately and expeditiously. This design, with practices randomized in a stepped-wedge fashion to a HTN QIC a) without subspecialist involvement, b) with subspecialist involvement and c) with pediatrician HTN diagnosis and management and subspecialist back-up, will also serve as a test case for whether pediatricians can diagnose and manage common chronic conditions (e.g., HTN) with a supporting subspecialist advisor. This proposal responds to AHRQ's Funding Opportunity Announcement PA-15-339, designed to develop evidence to improve safety in ambulatory care settings. This work is one of the first to test implementation of the new 2017 pediatric HTN guidelines and focuses on children in rural and urban settings, AHRQ priority populations.

Specific Aim 1: Determine whether a QIC in a national group of at least 60 pediatric practices, building on our prior elevated BP recognition work, is associated with reduction of errors in the broader outcomes of 1) HTN diagnosis, 2) initiation of management, and 3) time to diagnosis and management.

*Hypothesis 1: Practices randomized to a QIC will experience a 50% reduction in pediatric HTN and EBP diagnosis and management errors as compared to usual care.*

Specific Aim 2: Investigate whether a QIC with relevant, local pediatric HTN subspecialist involvement improves diagnosis and management for children with HTN.

*Hypothesis 2: Practices randomized to a collaborative with relevant, local HTN subspecialist involvement following participation in the original QIC, will experience an additional 15% reduction in pediatric HTN and EBP diagnosis and management errors as compared to the original QIC.*

Specific Aim 3: Determine whether pediatrician co-diagnosis and co-management of HTN, conducted via a 'hub and spoke' model where one pediatric HTN subspecialist advises multiple primary care pediatricians, improves diagnosis and management for children with HTN.

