### **3. Study Design, Cohort, and Methodology for Quality Improvement Collaborative (QIC):**

The goal of this proposal is to reduce the proportion of patients who experience pediatric HTN diagnosis and management errors, in order to reduce time to definitive management and therefore harmful sequelae often seen in children at the time of HTN diagnosis. We will accomplish this goal and test whether a QIC which assists teams in reliably performing evidence-based HTN processes, a QIC with integrated PCP and subspecialist participation, and/or a hub and spoke PCP-subspecialist care model can improve these measures via a prospective, cluster-randomized, stepped wedge design. In the primary outcome analyses, each of these 3 conditions will be compared to each other and to usual care. Diagnosing and managing pediatric HTN involves multiple steps, multiple visits, and multiple decisions, and the 2017 AAP guidelines have recently updated these practices. For this reason, and as demonstrated by the superior reduction in recognition of elevated BP error rates in this team's QIC as compared to [name] EHR intervention, an EHR intervention or best practice alert alone would be insufficient to drive this level of behavior change; a QIC is needed.

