## **6. Statistical Analysis**

### **6.1 Statistical Models:**

The primary independent variable will be interventions with titrated QIC dosage levels stepped-up from the control condition (usual care) with scale scores from 0 (usual care) to 3 (hub and spoke). The primary dependent variable will be the proportion of all incorrect diagnostic and management decisions completed per 100 patients with elevated BPs. The individual-level outcome will be binary (incorrect or correct care), and absolute risk difference will be the primary measure of intervention effects. As there will be a multilevel hierarchy in the data structure, we will apply generalized mixed-effects models with identity link for testing the primary hypothesis in terms of risk difference. Site-specific, practice group-specific, and month-specific intercepts will be considered random to take into account potential variations in outcomes at all such levels in addition to correlations of individual-level outcome nested within each month for each practice. We will test if each step-up of the interventions (QIC without subspecialist, QIC with subspecialist, and hub and spoke) as compared to the control condition significantly reduce incorrect diagnosis and management proportions. We will also make all pairwise comparisons among the four conditions including usual care. All analyses will be controlled for potential confounding effects including factors such as baseline error rates, patient volume, number and training of providers, nursing and office staff, and prior work improving these errors.

For the secondary analyses testing 1) time to care, 2) sustainability, 3) change in collaborative effect for second wave and 4) necessity of PCP and subspecialist integration before hub and spoke model introduction, we will use all relevant QIC data. Each of these hypotheses will be tested with appropriate contrasts between intervention effect and the relevant group and time in generalized mixed-effects regression models. Testing the sustainability will be based on a contrast within Cohort 1.

The main outcome will be presented with descriptive statistics, examining the percent of patients who accepted the HBPM and returned data in a timely manner. We will also analyze the concordance between in-clinic manual BP measurements and the HBPM measurement averages.

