### **6.3 Power Analysis:**

Assuming a two sided alpha level of 0.05 and >80% power, we calculated the effect size we could detect for the HTN and EBP diagnostic and management error primary outcome measure, comparing the three intervention conditions to the control condition and each other using the above models, and the QIC methodology and preliminary data (D.2.B.) presented in this application. As the data structure is complex with multilevel hierarchy in addition to introduction of titrated interventions in a stepped-wedge fashion, we conducted simulations to estimate empirical power to seek a minimally detectable effect size. We allowed substantial variations of the outcome at all levels of site, practice, and months. Specifically, we took 73% as the baseline diagnostic error rate under usual care and set the ranges of the outcome expectation as +/-15% at each level; for example, at the site level, the baseline incorrect diagnostic error rates will range from 73%-15% to 73%+15%, and so on. In addition, we set the outcome correlations among 10 chart reviews per month per site at a relatively large ICC=0.5. We used uniform distributions to randomly generate outcome expectations at all levels, and used Park's algorithm^92 to randomly generate individual chart-level correlated binary outcomes with ICC=0.5 for a given month. We generated 1000 simulation data sets for each candidate minimal effect size laid out in a grid search fashion and fitted the generalized mixed-effects model with random effect for all levels and counted p-values <0.05 out of 1000 for each effect size on the grid. As a result, our study with at least 7 practice groups, at least 60 sites, two cohorts, three intervention doses in addition to usual care, 24 months, and 10 chart reviews per month per practice is powered (>80%) to detect as small as 3% point decrease in each step-up 'titrated' dose, i.e., per each level increase in intervention dosage. Therefore, we are adequately powered to detect any decrease larger than 9% from usual care to hub and spoke condition.

Given the HTN error reduction estimates derived from our preliminary data and prior QIC, we are confident that we are powered to detect statistically and clinically significant effects in our primary outcome measure across all three intervention conditions.

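### The protocol calls every comparison among the four conditions primary, adds a dose slope on the same outcome, and uses an undivided 0.05 with no decisive test named

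*Protocol*

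**What the plan says.** The opening of Protocol section 3 states: "In the primary outcome analyses, each of these 3 conditions will be compared to each other and to usual care". Later in section 3, the paragraph on the merits of the stepped wedge design again calls the four-way comparison primary. It lists the second-wave and sustainability comparisons separately as secondary.

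Section 6.1 makes a dose score, 0 for usual care to 3 for hub and spoke, the primary independent variable. It refers to a primary hypothesis in the singular without saying which contrast that is. It then tests each intervention against usual care and adds: "We will also make all pairwise comparisons among the four conditions including usual care".

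Section 2 states three hypotheses with different comparators: QIC against usual care (1), QIC with subspecialist against the original QIC (2), and hub and spoke against QIC with subspecialist (3).

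Section 6.3 begins: "Assuming a two sided alpha level of 0.05 and >80% power, we calculated the effect size we could detect". The sentence goes on to cover "comparing the three intervention conditions to the control condition and each other using the above models". In the simulation the authors "counted p-values <0.05 out of 1000 for each effect size on the grid". The result is expressed per dose step: more than 80% power for a 3-point decrease. The protocol gives no order of testing, division of alpha or gatekeeping.

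**The concern.** The protocol defines a family of primary tests on one outcome and attaches an undivided 0.05 to it. A reader cannot tell which test decides whether the trial succeeded. If any significant member can be reported as a primary result, the chance of a false one exceeds 5%.

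The members also answer different questions. The slope asks whether errors fall on average as dose rises. Hypotheses 2 and 3 ask whether one specific step adds anything to the step before it. A significant slope can come entirely from the first step, so the test nearest to a lead role cannot support the claims about subspecialist involvement or hub and spoke.

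**Working it through.** **Counting the tests.** Four conditions give 4×3/2 = 6 pairs. The three contrasts with usual care are among these six. Adding the slope gives 7 distinct tests.

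**Inputs (section 6.3).** Error rate 73%; ICC 0.5 within a site-month; 10 charts per site-month; 60 sites; 7 practice groups; two cohorts; 24 months; variation of ±15 points at each level. Where baseline months are included, section 3 gives 3 months and section 4 gives 17 charts per month. Assumption: Cohort 1's sustain phase counts as hub and spoke.

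- Variance of a site-month mean: p(1−p)[1+(n−1)ICC]/n = 0.73×0.27×(1+9×0.5)/10 = 0.1971×5.5/10 = 0.108.
- Variance of a uniform ±0.15 effect: 0.30²/12 = 0.0075, used for group, site and month.
- Contrast covariances come from generalised least squares, (X′V⁻¹X)⁻¹.

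**The plan's own figure.** With month effects nested in site and no baseline months, the slope has SE 0.0093. Power is Φ(δ/SE − 1.96). At 3 points this is Φ(3.23 − 1.96) = 90%, and at 2 points 58%. So 3 points is the smallest whole-point step above 80%, as the protocol states. With a calendar-month effect shared by all sites, power at 3 points is only 38-50%, so the figure depends on how months were simulated.

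**Single steps in the same nested-month model.** A 3-point difference has power Φ(0.03/0.0344 − 1.96) = 14% for QIC against usual care, 22% for the second step (SE 0.0254) and 25% for the third (SE 0.0232). The stated power therefore does not carry over to the pairwise tests.

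**Family-wise rate if no intervention works.** This is P(max|Z| > 1.96), where Z is jointly normal with the correlations above (at least 400,000 draws).

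| Month effect | Six pairs | Six pairs + slope | Same, with baseline months |
|---|---|---|---|
| Nested in site | 19.7% | 20.5% | 20.8% |
| Random, shared by sites | 18.4% | 18.5% | 19.4% |
| Fixed | 14.1% | 14.1% | 15.0% |

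Four equal independent arms would give 20.3% for six pairs. The independence formula, 1 − 0.95⁷ = 30%, overstates because the tests are correlated. Counting only results in the direction of benefit, the rate is about 7-12%, against 2.5% for one two-sided test.

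**After the March 2020 stop.** The protocol does not say how far hub and spoke had been delivered. Both cases below are assumptions and include baseline months.

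- Twelve intervention months, so only usual care and the first two QIC conditions: three pairs plus slope give 12.4% (nested), 10.8% (shared) and 9.4% (fixed). In the benefit direction: 6.4%, 5.5% and 4.7%.
- Fourteen intervention months, so Cohort 1 has two hub-and-spoke months: all seven tests give 20.2% (nested) and 17.8% (shared).

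**What the slope can show.** Suppose QIC alone halves errors (73% to 36.5%) and later steps add nothing. The condition effects are 0, −36.5, −36.5 and −36.5 points. The unweighted slope on scores 0-3 is [(−0.5)(−36.5) + (0.5)(−36.5) + (1.5)(−36.5)]/5 = −54.75/5 = −10.95 points per level. In the trial's layout it is about −10 to −12, with z between −3.7 and −13. The slope is clearly significant although the true effects under Hypotheses 2 and 3 are zero.

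**The case against.** Multiplicity procedures are commonly left to the SAP, which is not shown, so the absence of a hierarchy alone would be no finding. That stands. The point rests instead on what the protocol fixes: section 3 twice calls all these comparisons primary, and section 6.3 attaches one undivided 0.05 to them.

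The slope can be read as the lead test. It is the primary independent variable, the pairwise tests are introduced as an addition, and the only power result is per dose step. This is the best reading available, and on it the lead test runs at 5%. But no sentence makes the slope decisive, and section 3 gives the pairwise comparisons the same standing.

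The protocol also never says that one significant test makes the trial positive. The family-wise rate describes what the wording permits, not a declared rule.

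Three stronger readings are tempting but not supported:

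- A reader might take 14-21% as the rate for the data to be analysed. It belongs to the planned 24 months. Section 3 says that design cannot continue and limits the analysis to November 2018 to March 2020.
- A reader might infer that, if only the first QIC works, the later conditions would be declared effective. Section 2 names the comparators for Hypotheses 2 and 3, and the pairwise tests include exactly those contrasts, whose true values would be zero.
- A reader might see a conflict because Aim 1 lists "1) HTN diagnosis, 2) initiation of management, and 3) time to diagnosis and management". Hypothesis 1 concerns errors only, and Table 2 and section 6.1 both treat time as secondary.

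**Conclusion.** The concern holds in limited form. The protocol sets up seven primary-labelled or co-equal tests at an undivided 0.05 without saying which decides. The resulting two-sided rate is about 14-21% for the full design and about 9-13% if only three conditions have data. False claims of benefit are about 7-12% and 5-7% respectively. The ranges reflect how months are modelled and whether baseline months enter. They assume that no intervention works and that any significant member of the family could be reported as primary. The post-stop figures also rest on an assumed amount of follow-up. The wording should be corrected before the collaborative data are reported; the point does not invalidate the design.

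**What to change.** In section 6.1, and in the two places in section 3 that use the word primary for all comparisons, limit the primary tests to the trial's own hypotheses in fixed order, each at two-sided 0.05:

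1. Hypothesis 1: QIC without subspecialist against usual care.
2. Only if that is significant, Hypothesis 2: QIC with subspecialist against QIC without.
3. Only if that is significant, and where data exist, Hypothesis 3: hub and spoke against QIC with subspecialist.

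Report the dose slope and the remaining pairwise contrasts as supportive estimates with 95% confidence intervals. State in section 6.3 that the power above 80% refers to the slope and not to single-step contrasts. Section 5 schedules unblinded interim analyses and monthly data review, so the amendment should record what data had been seen when the order was set.

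The change is to wording only. The sequence holds the family-wise rate at 5%, and Hypothesis 1 keeps its full alpha. There are two real costs. The slope, the only test with stated power, becomes supportive. No confirmatory claim is possible for Hypothesis 2 or 3 if an earlier step fails, and both are modestly powered. If their 15% reductions are read as relative (an assumption), the effects are 0.15×36.5 = 5.5 points and 0.15×31.0 = 4.7 points. In the nested-month 24-month model, power taken singly is Φ(5.475/2.54 − 1.96) = 58% and Φ(4.65/2.32 − 1.96) = 52%, before gating and before any loss of follow-up.

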### **6.2 Data Entry Errors and Missing Data:**

We will make every effort to minimize data recording errors by checking for outliers or abnormal values using frequency tables or graphical tools such as box plots. If noted, we will correct or check

the validity of those values and discuss with sites. Although we expect few by virtue of randomization, we will examine imbalances between groups with respect to baseline practice demographic characteristics and outcome measurements with standard statistical methods depending on the outcome scale and validity of normal distribution assumptions. If necessary, we will apply log-transformations for right-skewed data. We will include variables that are significantly different in the above statistical models to control for their potential confounding effects. Although we anticipate little missing data based on prior QICs, when noted, we will examine reasons for incomplete records. We will analyze available data as the primary analytic strategy since mixed-effects modeling is valid for missing at random data. However, if missing data rate is greater than 5%, we will also conduct sensitivity analyses applying a full conditional specification multiple imputation method which can apply to missing not at random data. We will compare results between available data analysis and multiple imputations data analysis.

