Although unlikely given the standard nature of primary and secondary outcome measures in this project, if any practice sites are unable to collect data for any reason, they will be coached and attempts will be made to facilitate data collection. If they are still unable to collect data, the stopping rules at which time the practice will be asked to leave the project will include inability to collect data for 2 months following data coaching interaction. It is incredibly unlikely that any Adverse Events or Serious Adverse Events will occur as part of this standard of care study. If any do occur, or an Unanticipated Problem occurs, the PI, [name], will take full responsibility, immediately report the event to the research team, the lead-site's IRB (Einstein/Montefiore), the local site's IRB, the Agency for Healthcare Research and Quality, and other appropriate offices or agencies as needed.

Finally, all data from all sites will be entered into a REDCap data base. Data capture will be centralized via direct patient data entry or electronic data transfers into this REDCap database. REDCap is web-based and HIPAA compliant, and [name] and Einstein/Montefiore will take responsibility for data security. These data will not include patient names, dates of birth, or medical record numbers. As noted above, we will employ an "honest broker" for our REDCap database with regards to clinic visit dates. [name] has functioned in this role before and will create 2 separate REDCap databases. Participating clinics will have access to and enter data in a REDCap database that includes visit dates. The research team will never have access to this database. The second REDCap database, accessible by the research team, will receive days elapsed between clinic

visit dates data from the first database, but no specific clinic visits dates. [name] will ensure the research team never receives any PHI from clinics.

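### Section 6.2 credits the imputation check with covering data missing not at random, but as described it assumes missing at random, like the primary model

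*Protocol*

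**What the plan says.** Protocol section 6.2 sets out three steps.

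- Primary strategy: "We will analyze available data as the primary analytic strategy since mixed-effects modeling is valid for missing at random data".
- Trigger: "if missing data rate is greater than 5%, we will also conduct sensitivity analyses". The method named for these is a "full conditional specification multiple imputation method which can apply to missing not at random data".
- Use of the result: "We will compare results between available data analysis and multiple imputations data analysis".

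The section expects little missing data, gives no rate, and says that reasons for incomplete records will be examined. Section 6.1 defines what would be imputed: "The individual-level outcome will be binary (incorrect or correct care), and absolute risk difference will be the primary measure of intervention effects". Neither section 6.2 nor any other part of the protocol mentions a shift parameter, a pattern-mixture or selection model, or a worst-case imputation.

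**The concern.** Full conditional specification is a way of building imputation models one variable at a time. Each model is fitted to records where the variable is observed and then used to fill in the records where it is not. Unless the analyst adds something, a missing outcome is assumed to behave like an observed one with the same values of the other variables. That is missing at random. The method can be carried over to data missing not at random only by adding an explicit departure, and the protocol mentions none.

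The plan therefore describes a comparison of two analyses under missing at random while attributing to one of them a wider reach. If they agree, a reader who relies on section 6.2 would take the agreement as evidence that the result withstands loss that depends on the outcome. It would be no such evidence.

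**Working it through.** The protocol gives no figure to reproduce here, so the check has three parts: a comparison of assumptions, a simple bound, and a simulation.

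**1. Assumptions side by side (section 6.2)**

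| Analysis | Stated basis | Assumption as described |
|---|---|---|
| Available-data mixed model | Valid under missing at random | Missing at random given the model's variables |
| Full conditional specification imputation | Said to reach missing not at random | Missing at random given the imputation model's variables; no departure term |

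The conditioning sets may differ. The class of assumption does not.

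**2. Simple bound (assumed inputs)**

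Shift in one condition's error rate = fraction missing × (true rate in missing charts − imputed rate).

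- At the protocol's 5% trigger with an assumed 20-point gap: 0.05 × 20 = 1.0 point.
- At an assumed 15% missing with the same gap: 0.15 × 20 = 3.0 points.

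For scale, section 6.3 gives 3 percentage points per step as the smallest detectable effect.

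**3. Simulation**

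From the protocol: usual-care error rate 73% (section 6.3, "we took 73% as the baseline diagnostic error rate under usual care"), and a 50% relative reduction under the collaborative (section 2, Hypothesis 1), so 0.5 × 73% = 36.5% and a risk difference of −36.5 points.

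Assumed: 60 sites with 60 charts each, site effects of ±10 points, one covariate, 10 imputations and 30 replicates. Outcomes were missing with probability 5%, except for intervention charts with an error, where it was 8%, 20%, 30% or 40%. The analysis was a simple difference in proportions, not the full mixed model. The last column adds to the imputation a log-odds shift set to its true value.

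| Missing overall | Full data | Available data | Standard imputation | Imputation with true shift |
|---|---|---|---|---|
| 5.4% | −0.3688 | −0.3780 | −0.3782 | −0.3711 |
| 7.7% | −0.3653 | −0.4033 | −0.4029 | −0.3654 |
| 9.4% | −0.3662 | −0.4326 | −0.4320 | −0.3663 |
| 11.4% | −0.3678 | −0.4673 | −0.4661 | −0.3682 |

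Available data and standard imputation differ by 0.02 to 0.12 points on average, while both miss the full-data value by about 1 to 10 points. With the true shift, the imputation comes within about 0.2 points of full data in every row.

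**4. How severe these scenarios are**

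Take the 7.7% row. In the intervention condition:

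- Fraction missing = 0.365 × 0.20 + 0.635 × 0.05 = 0.1048.
- Error rate in missing charts = 0.073 / 0.1048 = 69.7%.
- Error rate in observed charts = 0.292 / 0.8953 = 32.6%.
- Gap = 37.1 points, and 0.1048 × 37.1 = 3.9 points, in line with the simulated 3.8.

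The simulation therefore obeys the formula in step 2, with a larger assumed gap. It shows how the comparison behaves under such loss, not how likely such loss is.

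**The case against.** The strongest defence is the verb. The protocol says the method can apply, and with an added shift it can; the fix proposed here keeps the imputation and adds one. The imputation model and the size of any shift are also details that a statistical analysis plan, not shown here, would normally hold. Their absence is not the point. What remains is that the protocol attributes the property to the method as named, mentions no extension, and plans only a direct comparison with the primary analysis.

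Second, imputation need not simply duplicate the primary analysis. The chart review tool collects age, race, insurance, blood pressure values and the count of earlier elevated visits. Missing at random given these is a different and often more plausible condition. That is correct, and it is why the point concerns the class of assumption and not identical results. It does not reach missing not at random, and a chart that was never submitted may bring none of these variables.

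Third, the exposure may be small. Little missing data is expected, the check runs only above 5%, and the data collection guidance scores undocumented items as not done, so many gaps in a chart never become a missing outcome. This limits the importance of the point but does not make the sentence right.

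Two stronger readings are tempting, and the documents support neither.

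- A reader might infer that poorly performing sites are likelier to be missing, because in the data and safety monitoring plan "the stopping rules at which time the practice will be asked to leave the project will include inability to collect data". That rule is introduced as unlikely to be needed, follows coaching and a further 2 months, and concerns capacity to collect data. Nothing links it to error rates. Withholding central feedback from Cohort 2 is likewise not shown to cause missing data.
- A reader might infer that the pandemic caused loss that depends on the outcome. The protocol describes a pause of the whole study in March 2020, which truncates follow-up for everyone.

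**Conclusion.** The point holds as a wrong statement about a method. As section 6.2 is written, both analyses assume missing at random, and their agreement cannot support the claim made for the imputation.

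The size is conditional. The 20-point gap, its confinement to one condition, the 15% missing rate and the simulation's missingness probabilities are all assumptions. Read as relative reductions, the hypothesised effects are 36.5 points for the first step, 0.15 × 36.5 = 5.5 for the second and 0.15 × 31.0 = 4.7 for the third. A 1.0-point shift would matter little to the first. A 3.0-point shift would be a large part of either later step.

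The primary analysis and the power calculation are not affected. The correction is worth making before the missing-data results are interpreted, but the point is not a reason to doubt the trial's main result.

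**What to change.** In section 6.2, replace the clause that credits the imputation with covering data missing not at random. Wording to this effect would do:

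> Multiple imputation by full conditional specification assumes missing at random given the variables in the imputation model, which will reflect site and month. If more than 5% of outcomes are missing, imputed error probabilities will also be shifted over a pre-stated range, separately by condition, and the shift at which the conclusion changes will be reported.

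A range such as +5, +10 and +20 points would be a reasonable start, fixed before results are compared. The top of the range needs care. Section 6.3 allows site-level rates up to 73% + 15% = 88%, and 88% + 20% exceeds 100%, so either cap the shifted probability or define the shift on the log-odds scale. Carrying site and month into the imputation matches the random effects in section 6.1.

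The cost is a sentence or two and a little programming, with no new data. The range remains a matter of judgement, and the result is a short table instead of a single comparison.
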